## Abstract

**Background::**

Mental health is closely related to the occurrence of hypertension, particularly the prognosis of hypertension patients. The role of psychotherapy in the occurrence, development, prevention, and prognosis of hypertension, remains to be clarified.

**Methods/design::**

We will conduct a prospective, double-blind, randomized, multiple-centers study. Eighty patients enrolled in this trial will be randomized at 1:1 ratio. The primary endpoint is will be the reduction of the patient psychological scale (PHQ-9) score. Secondary endpoints will be the drop in blood pressure, awareness of physical and mental health and self-efficacy scale. Measurements will be performed at baseline, 5-week (questionnaires only), 10-week (primary endpoint), using the Anxiety Screening Questionnaire (GAD-7) and Depression Scale (PHQ-9). Data analysis will be carried out using the SPSS v.25 software assuming a level of significance of 5%. Results will be analyzed using multilevel, regression analysis and hierarchical linear models.

**Discussion::**

We hope to provide some insight in the understanding the underlying mechanism of the novel mindfulness in the management of hypertension related psychological stress/disturbance, and will enable us to develop novel approach to manage essential hypertension and its related psychological disorders.

**Clinical trial registry::**

http://www.chictr.org.cn (ChiCTR1900028258)

## Introduction

1

With the change of the “biological-psychological-social” medical model, it is agreed that essential hypertension (EH) is a typical psychosomatic disease. EH accounts for about 90% to 95% of hypertension patients. The prevalence of hypertension in adults (18 years) is 27.9% in China.^[1]^ The number of hypertension patients is exceeded 270 million. The prevalence of hypertension is doomed to increase in the next few decades, due to increase longevity and lifestyle changes.^[2]^ In addition to the body itself or genetic factors, the psychological factors contribute to occurrence of hypertension. Hypertension caused by long-term depression and anxiety, compromises the quality of life and poor prognosis.^[3]^ It has been demonstrated that the patients with cardiovascular disease have a higher incidence of psychological disorders, as well as increased risk of central cerebrovascular accidents in people with anxiety and depression.^[4]^ Psychological stress increases the risk of developing high blood pressure, which also positively contributes to the high incidence of psychological and behavioral disorders.^[5]^ Some overseas studies demonstrate that the prevalence of depression, anxiety disorder or the mixed is 10.3%, 27.1%, or 4.5%, respectively.^[6]^ On the other hand, The Chinese Mental Health Survey shows that the prevalence of anxiety or mood disorders is 7.57%, or 7.37%, respectively.^[7]^ Thus it is logical to understand that the hypertension patients are vulnerable with mental health problems.^[8]^

Hypertension, a lifelong disease, is often accompanied with left ventricular hypertrophy, coronary heart disease and stroke and kidney failure. The management of hypertension is rather lengthy challenge, often requires patient life-time self-management.^[9]^ Because hypertension is a life-time disease, these patients may lead to ideological burden and psychological stress.^[10]^ It is well known that hypertension patients are more likely to have negative emotions such as fear, anxiety, and depression.^[11]^ However hypertensive patients with psychological problems (such as depression or anxiety) are often not to stick to medication, leading to unstable blood pressure, more prone to complications, and finally lowering the quality of life.

Hypertensive patients often experience negative emotions with anxiety and depression during treatment and are often in a state of survival, further exacerbating their negative emotions.^[12]^ Thus, to solve these negative emotions is a key in improving the quality of life. Mindfulness-based cognitive therapy is mainly use to explore the effectiveness of treatment of hypertension with anxiety and depression,^[13–15]^ reducing stress through mindfulness, and adjusting the psychology to achieve the effect of reducing blood pressure.^[16,17]^ Cognitive behavioral therapy (CBT) is widely used in treatment of hypertension patients, because of its advantages of wide benefit and high efficiency. CBT provides face-to-face communication opportunities and, makes the patients familiar with the environment quickly to increases the sense of security and reduces their discomfort. Although the research on mindfulness based stress reduction is not rich, it describes an alternative approach for physicians to help these patients cope with their condition more effectively.

The research of CBT for hypertension patients in China is at the initial stage. The problems include a relatively small sample, non-standard mindfulness interventions, and a high rate of loss. In addition, the researchers only focus on Explain whether hypertension is effective without quantitation of hypertension value, nor epidemiology. Thus ideally the research should be focusing on the mechanism of mindfulness therapy in the anti-hypertension with objective quantification analysis.

## Methods/design

2

### Trial design

2.1

This study is designed as a prospective, double-blind, randomized, multiple-center study with 10 weeks duration. The protocol scheme (Figs. 1 and 2).

**Figure 1 F1:**
[figure not shown]
Protocol scheme of the study.

**Figure 2 F2:**
[figure not shown]
The schedule of enrolment, interventions, and assessments.

### Aim of the study

2.2

The objective of this study is to perform comprehensive psychosomatic promotion in hypertension patients with anxiety and depression for improvement of their physical and mental health status. Furthermore we also promote the awareness of physical and mental health knowledge, particularly in self-management.

### Eligibility criteria of the participants

2.3

#### Inclusion criteria

2.3.1

1.Hypertensive patients (systolic blood pressure > 140 mmHg, and/or diastolic blood pressure > 90 mmHg)2.Depression scale (PHQ-9) evaluation score ≥ 5 points3.Aged 18 to 69 years4.Understand the questionnaires without obvious barriers to daily communication5.Stay in the current residence within the next 6 months.

#### Exclusion criteria

2.3.2

1.Patients are with severe myocardial infarction, cerebral infarction, cirrhosis, uremia2.Physically unable to participate in the project activities3.Vision and hearing were severely impaired, and physical activity is limited affecting participants4.Taking anti-psychotics, anti-anxiety and depression medications within 3 months5.Taking self-reported with substance abuse and Alzheimer's disease.

### Discontinuation criteria

2.4

1.Disease progression or death.2.Patient refusal.3.Other reasons of unsuitability owing to which the study protocol should not continue.

### Enrollment, randomization and blinding

2.5

We plan to recruit 80 cases and actually 60 people; patients will be randomized at 1:1 ratio in the Gansu Gem Flower Hospital. The study participants do not know their grouping, the outcome assessors and the analyst do not know the grouping of the research objects, are responsible for collecting the baseline data, the physical examination, questionnaire survey at the end of the study, and conducted data entry and statistical analysis. The blinding codes will place in a sealed envelope and will be revealed only when adverse events occur or at the terminal analysis.

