### Sample size calculation

2.10

The sample size will be calculated by PASS software based on the difference test formula for 2 samples mean comparison in group randomized controlled trial. The indicators will be selected as follows:

(1)The error setting is 1−*β *=* *0.9, *α *=* *0.05.(2)Sample size setting: There are two groups for each community in the intervention group and the control group, with about 30 people in each group. The number of communities in the intervention group and the control group is same.(3)Effect scale setting: there is no change in the control group after the intervention, and the mean change is calculated based on the anxiety end-line and baseline difference of the intervention group in the pretest hypertension patients. Intragroup correlation was set to 0.01.

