### Limitations of this study

2.14

Intrinsic and extrinsic factors influencing physical and mental health factors are diverse, therefore, the relative importance of circumstances may vary with time and this needs to be considered when designing the programs and policy interventions.

The current study will be performed in 3 areas of Lanzhou, which doesn’t necessarily reflect the entire country, the possible treatment bias may not be excluded completely.

Moreover, we realize that the intervention implementation process, team training, different times, resources and adaptations, may have some impacts to the outcomes of the study.

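### The protocol states two conflicting sample sizes, 80 and 60, and its 90% power is tied to neither

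*Protocol article*

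**What the plan says.** Three places in the protocol article bear on the number of patients.

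- **Abstract, Methods/design:** "Eighty patients enrolled in this trial will be randomized at 1:1 ratio".
- **Section 2.5, Enrollment, randomization and blinding:** "We plan to recruit 80 cases and actually 60 people; patients will be randomized at 1:1 ratio in the Gansu Gem Flower Hospital". It does not say whether 60 is a number enrolled, eligible, randomised or expected to finish.
- **Section 2.10, Sample size calculation:** the method is described as "based on the difference test formula for 2 samples mean comparison in group randomized controlled trial", with "The error setting is 1−*β *=* *0.9, *α *=* *0.05" and an intragroup correlation of 0.01. On structure it says: "There are two groups for each community in the intervention group and the control group, with about 30 people in each group". It adds: "The number of communities in the intervention group and the control group is same". It gives neither a total nor a number of communities.

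Section 2.14 says: "The current study will be performed in 3 areas of Lanzhou". Nothing in the article equates an area with a community in the sense of 2.10.

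**The concern.** The number randomised is the figure to which enrolment, the planned analysis count and the power claim all refer. Here the Abstract and section 2.5 disagree about it, and the sample size section settles the matter for neither.

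Each way of understanding the 60 requires a change to the text. If 60 are randomised, the Abstract is wrong. If 80 are recruited and 60 of them prove eligible, the Abstract is still wrong, because it has 80 randomised. If 60 are expected to provide final data, the plan assumes a loss that it does not state.

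The difference also matters for the analysis. Section 2.7 makes all randomised patients the primary population, and then drops missing data endpoint by endpoint. Whether 60 is the randomised or the evaluable number decides how many patients the primary comparison is planned to rest on.

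**Working it through.** **1. Can the plan's own figure be reproduced?** No. Section 2.10 takes its effect from a pretest change and prints neither the mean change nor a standard deviation, so neither 80 nor 60 can be derived from it. A condensed article may leave those inputs to the full protocol. What can be checked is whether the printed numbers agree.

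**2. Does the group structure in 2.10 give 80?** Inputs: about 30 people per group, and equal numbers of communities per arm.

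- One intervention and one control group in one community: 2 × 30 = 60.
- Two groups in each arm, one community per arm: 2 × 2 × 30 = 120.
- Working back from 80: 80/30 = 2.67 groups. Two groups would need 40 each and four groups 20 each, neither of which is about 30.

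So the structure can match 60 on one reading, and it does not match 80 on either.

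**3. Can loss to follow-up link the two numbers?** 1 − 60/80 = 0.25, and 60/(1 − 0.25) = 80. A 25% loss would connect them exactly, but no loss rate is stated.

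**4. What would the difference mean for power?** This is an illustration only. Assumptions: 1:1 allocation, two-sided α = 0.05 (2.10 does not give the sidedness), normal approximation, n per arm, standardised effect d.

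Effect detectable with 90% power: d = (1.960 + 1.282) × √(2/n).

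- n = 40 (total 80): d = 3.242 × 0.2236 = 0.725
- n = 30 (total 60): d = 3.242 × 0.2582 = 0.837

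Power for a given d: Φ(d/√(2·DE/n) − 1.960). DE is 1 without clustering. With the intragroup correlation of 0.01 and groups of 30, DE = 1 + 29 × 0.01 = 1.29. The design effect is derived here; the protocol does not print it.

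| Assumed basis of the 90% | Power at 80 | Power at 60 |
|---|---|---|
| Sized at 80, clustering treated alike in sizing and analysis | 90% | Φ(2.807 − 1.960) = 80% |
| Sized at 80 without clustering, DE 1.29 then applies | Φ(2.854 − 1.960) = 81% | Φ(2.472 − 1.960) = 70% (69% with the t distribution) |
| Sized at 60, clustering treated alike in sizing and analysis | 96% | 90% |

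The second row needs caution. Forty per arm is not a whole number of groups of 30. Thirty per arm is a single group per arm, where variation between groups cannot be separated from the treatment effect. A simple design effect then shows only the direction and rough size of the loss.

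**The case against.** The strongest reply accepts the 80 versus 60 conflict and disputes anything built on it.

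- **A required total of 120 or more.** A reader might infer from 2.10 that at least 120 are needed, or 180 over the three areas (3 × 2 × 30). The document does not support this as a stated or minimum size. The sentence on communities does read as if communities belong to arms, which leans towards two groups per arm. But one group per arm in one community is also a possible reading, and it gives 60. The figure of 180 further needs areas to be communities, which is nowhere said. There are two stated sizes and one ambiguous description, not three stated sizes.
- **Power that cannot hold.** A reader might infer that 90% power is impossible for all the candidate totals. Without an effect size this is not shown. A trial sized for 90% at 60 has at least 90% at 80 and at 120 when clustering is treated consistently. Only exactly 90% at more than one total is impossible, and the protocol does not claim that.
- **An undefined analysis population.** Section 2.7 defines it as all randomised patients. The planned count is unclear; the definition is not.
- **Missing inputs.** The effect, standard deviation, number of clusters and loss rate may stand in the full protocol. Their absence from an article is not the point here.
- **An innocent explanation.** 60 may be 80 less 25% loss, and the Introduction notes high loss in earlier Chinese research. That is plausible, but the text does not say it.

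All of these replies stand. None removes the contradiction between the Abstract and 2.5, or the lack of any link from the 90% power to either number.

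**Conclusion.** The concern holds in limited form. The article gives 80 as the number randomised in one place and sets 80 beside an unexplained 60 in another. The group structure in 2.10 does not produce 80 on either simple reading. The 90% power can be attached to neither number.

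This conclusion needs no assumption about the effect. The size of the consequence does. If 80 was the basis, randomising or analysing 60 lowers power from 90% to about 80%. If clustering was also left out of the sizing, power is roughly 81% at 80 and 69 to 70% at 60. If 60 was the basis and clustering was treated consistently, nothing is lost. The article does not show which case applies, so it does not establish that the trial is underpowered. It is still worth correcting before the number is relied on, because it concerns the enrolment target and the one power claim in the plan.

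**What to change.** - State one randomised total, the same in the Abstract, 2.5 and 2.10.
- Say what 60 denotes. If it is the number randomised, correct the Abstract. If it is the number expected with week-10 data, say so and state the 25% loss.
- Rewrite the sentence on groups per community so that the number of groups times their size equals the total, and give the number of communities.
- Restate the power, or the detectable difference, for the number to be analysed, using the pretest effect and standard deviation already used in the calculation. The illustrative effects above should not be taken over as replacement text.

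The cost is wording and a rerun of an existing calculation. The restated power may be less favourable than 90%; until the pretest figures are applied, the direction is not known.

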### Background data

2.6

The patients’ background data are collected prospectively, including sex, age, history, complications, past treatments for hypertension. The results of the project are only published in groups, and no personal information will be published; the information of the questionnaire you fill out will be kept in a safe and reliable place and will not be disclosed to members outside the research team. We will strictly protect your personal information. The data was obtained by contacting the corresponding author 6 months after the test results were published. Monitoring will be performed annually by each dataset to evaluate and improve study progress and quality.

### Statistical analysis

2.7

The primary population for efficacy analysis is the intention-to-treat population, defined as all randomized patients. The stratified OR will be estimated by logistic regression analysis with randomized factors as covariates, and multivariate regression analysis will be used to explore interactions between therapies and back-ground factors. Linear models will be used to test for between group differences in the continuous outcome measures. Secondary endpoints are summarized using 

 and frequency. Missing data will be excluded from the analysis of the corresponding endpoint.

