### Outcomes

2.9

Primary endpoint is the psychological scale score. Secondary endpoints are blood pressure in these patients, awareness of physical and mental health, and self-management efficiency. We will measure these parameters separately in three time-points, that is, base, mid court (the fifth week), and final lines. We will evaluate the psychological scale score, blood pressure, physical and mental health awareness and self-efficacy at week 10.

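### Section 2.7 specifies a stratified odds ratio with no binary outcome or strata, next to linear models, and does not say which decides the primary PHQ-9 comparison

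*Protocol article*

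**What the plan says.** Section 2.7 (Statistical analysis) takes all randomised patients as the primary efficacy population. Its next sentence begins: "The stratified OR will be estimated by logistic regression analysis with randomized factors as covariates". No outcome is attached to this odds ratio, and the factors are not listed. The sentence after that reads: "Linear models will be used to test for between group differences in the continuous outcome measures".

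Elsewhere the article treats the primary endpoint as a score:

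- Abstract, Methods/design: the primary endpoint "will be the reduction of the patient psychological scale (PHQ-9) score".
- Section 2.9 (Outcomes): "Primary endpoint is the psychological scale score".
- Section 2.10 (Sample size calculation): the basis is the "difference test formula for 2 samples mean comparison".
- Abstract, on analysis: "Results will be analyzed using multilevel, regression analysis and hierarchical linear models". No odds ratio is mentioned.

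The only PHQ-9 threshold is an entry criterion in section 2.3.1: "Depression scale (PHQ-9) evaluation score ≥ 5 points". Section 2.5 gives a 1:1 ratio and no stratification factor.

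**The concern.** Logistic regression needs a categorical outcome, and a stratified estimate needs strata. The article defines neither, so the odds-ratio sentence cannot be carried out as written.

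The position of the sentence adds to the difficulty. It follows directly on the definition of the primary efficacy population, so a reader may take it as the efficacy analysis. The linear-model sentence covers continuous outcomes in general, blood pressure as well as PHQ-9, and is not labelled primary either.

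At stake are two choices that should not be open once data are seen: which effect measure counts (a mean difference or an odds ratio) and, if the odds ratio, at which PHQ-9 cut-point. A choice made with sight of the group results can inflate the false-positive rate. Even a cut-point fixed in advance would lose information and would not match the two-means basis of the sample size.

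**Working it through.** **1. Does each stated analysis have an endpoint to run on?**

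| Element | Stated in | Type | Fits the odds ratio? | Fits the linear model? |
|---|---|---|---|---|
| PHQ-9 reduction | Abstract | continuous | only after a cut-point | yes |
| Psychological scale score | 2.9 | continuous | only after a cut-point | yes |
| Sample size on two means | 2.10 | continuous | no | yes |
| Blood pressure | Abstract, 2.9 | continuous | only after a cut-point | yes |
| Awareness; self-efficacy or self-management | Abstract, 2.9 | not stated | not stated | not stated |
| PHQ-9 of at least 5 | 2.3.1 | entry criterion, not an outcome | no | no |

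The linear model fits the primary endpoint and the sample-size basis. The odds ratio fits no endpoint as defined.

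**2. The planned N.** The article gives power 0.90, alpha 0.05, an intragroup correlation of 0.01, groups of about 30, and N as 80 planned and 60 actual. It gives no number for the effect or the SD, so N cannot be reproduced. It can only be inverted, and sidedness (not stated) is assumed to be two-sided:

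d = (1.960 + 1.282) × √(2/n), with n per arm.

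- N = 80, n = 40: d = 3.242 × 0.2236 = 0.725 SD
- N = 60, n = 30: d = 3.242 × 0.2582 = 0.837 SD

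With the design effect 1 + (30 − 1) × 0.01 = 1.29, multiply by √1.29 = 1.136. This gives 0.823 SD (N = 80) and 0.951 SD (N = 60).

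**3. Cost of dichotomising, if it were done (illustration).** For a normal outcome cut so that a proportion q lies on one side, the information kept relative to the mean comparison is φ(c)²/[q(1 − q)], where c is the normal quantile of q:

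- q = 0.5: 0.3989²/0.25 = 0.637
- q = 0.3: 0.3477²/0.21 = 0.576
- q = 0.2: 0.2800²/0.16 = 0.490

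To get power, take the unclustered d from step 2 and an assumed control response rate. The response rate in the trial arm is 1 − Φ(c − d), where c is now the cut that gives the control rate. Power is that of a two-proportion normal test:

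| N | d (SD) | Control response (assumed) | Trial-arm response | Power on means | Power, two proportions |
|---|---|---|---|---|---|
| 80 | 0.725 | 0.50 | 0.766 | 0.90 | 0.700 |
| 80 | 0.725 | 0.30 | 0.579 | 0.90 | 0.719 |
| 80 | 0.725 | 0.20 | 0.454 | 0.90 | 0.683 |
| 60 | 0.837 | 0.50 | 0.799 | 0.90 | 0.688 |
| 60 | 0.837 | 0.30 | 0.623 | 0.90 | 0.718 |
| 60 | 0.837 | 0.20 | 0.498 | 0.90 | 0.687 |

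A variant with n = 40 per arm, d = 0.734 (from the t-test), the cut midway between the arm means and the arcsine formula gives 0.738. The range is therefore about 68–74%.

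**The case against.** The strongest reply is that PHQ-9 is continuous and section 2.7 assigns linear models to continuous outcomes. The abstract's hierarchical linear models and the two-means sample size point the same way. On that reading the primary analysis exists and can be run. This stands.

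A reader might infer that the odds ratio is the lead efficacy analysis, so that the primary comparison cannot be run or an after-the-fact cut-point is forced. The document does not support that. It never calls the odds ratio lead, primary or main; it is only listed first. Nothing in the text requires PHQ-9 to be dichotomised. The odds ratio may be meant for another outcome: section 2.7 summarises secondary endpoints partly by frequency, and awareness could be categorical, although the article does not say so.

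Two further points carry some weight. A condensed article may leave stratification factors to the full protocol, so their absence here does not show that none exist. Section 2.5 keeps the analyst unaware of grouping and the codes sealed, barring adverse events, until the terminal analysis. That reduces the risk of a cut-point picked on group results, but does not remove it.

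What the reply leaves unanswered is the mismatch in the stated text. An effect measure is promised that matches no defined endpoint, it stands beside a different effect measure, and neither is named as decisive for PHQ-9. That is more than detail left to an analysis plan.

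**Conclusion.** The point holds as an ambiguity in the stated text. Section 2.7 specifies a stratified odds ratio with no binary outcome and no stated strata, together with linear models, and does not say which one settles the primary PHQ-9 comparison. It should be fixed. It is not a fatal flaw, because a suitable analysis is already named.

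The size is conditional. If PHQ-9 were dichotomised, a median split would keep about 64% of the information, and power would fall from 90% to about 68–74%. These figures assume a normal outcome, two-sided 5% testing, individual randomisation (the intragroup correlation of 0.01 ignored), assumed response rates or cut position, and an effect back-solved from N = 80 or 60. They show what such a choice would cost; they are not a loss that the protocol prescribes.

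**What to change.** In section 2.7, state that the primary analysis is the between-group mean difference in PHQ-9 at week 10, adjusted for baseline PHQ-9, with 95% CI, from the linear (mixed) model already named. Use the same wording for the endpoint in the abstract and section 2.9.

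Then either delete the stratified odds ratio, or keep it as a secondary analysis of a named binary outcome, with the cut-point and the covariates written down before unblinding. If the randomisation did use strata, list them in section 2.5 so that the randomised factors have a referent.

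The cost is one or two sentences of text. It needs no new data, patients or sample-size calculation, since the mean difference already matches the two-means basis of section 2.10.

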### Informed consent

2.11

Signed informed consent will be obtained from all of the enrolled patients. Any of these participants can withdraw from the study without restrictions. The data collected up to the time of withdrawal will be included in the analysis unless participants specifically request for their data to be withdrawn.

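### Excluding missing data turns the week-10 PHQ-9 comparison into a complete-case analysis, although section 2.7 names all randomized patients as the primary population

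*Protocol article*

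**What the plan says.** All places are in the Protocol article.

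- **Section 2.7, population:** "The primary population for efficacy analysis is the intention-to-treat population, defined as all randomized patients".
- **Section 2.7, last sentence:** "Missing data will be excluded from the analysis of the corresponding endpoint". For continuous outcomes the same section names linear models for the between-group test.
- **Abstract, endpoint and timing:** "The primary endpoint is will be the reduction of the patient psychological scale (PHQ-9) score". The scores are taken at three times, and week 10 is marked as primary: "Measurements will be performed at baseline, 5-week (questionnaires only), 10-week (primary endpoint". The Abstract also names multilevel and hierarchical linear models.
- **Section 2.11, withdrawal:** "The data collected up to the time of withdrawal will be included in the analysis unless participants specifically request for their data to be withdrawn".
- **Section 2.4, discontinuation:** the list opens with "Disease progression or death" and continues with refusal and other unsuitability. It does not say whether a discontinued patient is still assessed at weeks 5 and 10.
- **Introduction:** among the problems of earlier Chinese studies it lists "a high rate of loss".

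**The concern.** The two statements in section 2.7 cannot both hold for the primary endpoint once any week-10 PHQ-9 is missing. The population is everyone randomized, but the comparison is made only among those who supplied the final score.

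The article chooses this rule itself, so it is not a detail left to an unseen analysis plan.

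Two things are at stake. First, patients with a final score are no longer the groups that randomization formed. If the reason for loss is tied to how patients are doing, and the arms differ in how many such patients they lose, the primary difference is distorted. The arms receive different programmes (section 2.8), so unequal loss is plausible, and the Introduction shows that the authors know loss is a problem in this field. Second, the trial collects a week-5 PHQ-9 that says something about patients who leave later, and the exclusion rule makes no use of it.

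**Working it through.** **1. What each rule does with the same patient.** Take a patient with PHQ-9 at baseline and week 5 who leaves before week 10.

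| Source | Treatment of this patient |
|---|---|
| Section 2.7, population | In the primary analysis |
| Section 2.7, missing-data rule | Out of the week-10 comparison |
| Section 2.11 | Scores up to withdrawal are in the analysis, unless removal is requested |
| Abstract, multilevel models | Can be in, if the model is fitted to all observed scores |

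The first two rows contradict each other. The third is in tension with the second, and the fourth shows a way to resolve it.

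**2. Is there a figure in the plan to reproduce?** No. The article gives no loss rate for this trial, no SD and no missing-data calculation. Everything below rests on assumed inputs and is expressed in SD units.

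**3. Size of the possible bias, by formula.** Assume normally distributed scores with SD 1, higher being worse. Correlations are assumed to be 0.5 between baseline and each later visit and 0.7 between weeks 5 and 10. Suppose the worst-scoring share p of an arm is lost. If loss follows the week-10 score, the mean of those remaining is too low by

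shift(p) = φ(z₁₋ₚ) / (1 − p).

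- p = 0.20: 0.280 / 0.80 = 0.350
- p = 0.05: 0.103 / 0.95 = 0.109
- Difference between arms: 0.350 − 0.109 = 0.241 SD

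If loss follows the week-5 score, the shift carries over to week 10 through the correlation: 0.7 × 0.241 = 0.169 SD.

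With equal p in both arms the shifts cancel and the difference is 0.

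**4. Check by simulation** (400,000 patients per arm, true benefit 0.50 SD). The last column uses baseline and week 5 for all randomized patients through a regression within each arm, standing in for a likelihood-based longitudinal model.

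| Loss control / intervention | Driven by | Complete case | Complete case, baseline-adjusted | Using week 5 |
|---|---|---|---|---|
| 10% / 10% or 20% / 20% | either score | 0.50 | 0.50 | 0.50 |
| 20% / 5% | week 10 | 0.26 | 0.31 | 0.34 |
| 20% / 5% | week 5 | 0.33 | 0.39 | 0.50 |
| 5% / 20% | week 10 | 0.74 | 0.70 | 0.66 |
| 5% / 20% | week 5 | 0.67 | 0.62 | 0.50 |

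The unadjusted bias is 0.17 to 0.24 SD, as in step 3. Baseline adjustment reduces it to 0.12 to 0.20 SD. Greater loss of poor scorers among controls hides benefit, and greater loss in the intervention arm inflates it. With no true effect the same loss patterns produce a spurious difference of the same size.

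**5. What the week-5 scores buy.** When loss depends on observed scores, using them removes the bias. When it depends on the unseen week-10 score, about 0.16 SD remains (0.50 − 0.34, or 0.66 − 0.50).

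**The case against.** The strongest defence is that the documents can be read consistently. Section 2.11 keeps data that were collected, and section 2.7 leaves out data that were not. A multilevel model of all observed PHQ-9 scores would satisfy both, and the Abstract names such models. This stands in part: the conflict with section 2.11 is not strict. It does not rescue section 2.7, which names only linear models with exclusion by endpoint. Nor does the Abstract say that its levels are visits within patients. Section 2.10 sets an intragroup correlation of 0.01, so the levels could equally be patients within groups.

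A second defence is that no bias has been shown. That is correct: the article states no loss rate, imbalance or mechanism, so the rule can bias the comparison but need not.

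Three stronger readings are tempting, and the documents do not support them.

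- **That patients stopped for disease progression are removed from the primary analysis, and are those doing worst.** Section 2.4 does not say that they miss the week-10 questionnaire. Progression is undefined and, in a hypertensive population, need not mean a worse PHQ-9. The criterion applies to both arms.
- **That a quarter of patients will be lost.** Section 2.5 mentions 80 and 60, and 1 − 60/80 = 25%. But that sentence is about recruitment, and section 2.10 separately speaks of about 30 per group. Neither gives an attrition rate.
- **That the bias is known to favour the intervention.** With an assumed SD of 4 points, a bias of roughly −0.9 or −0.7 point appears if dropout follows worsening in the intervention arm only and is random among controls. Nothing in the article supports that asymmetry. Under one dropout rule for both arms the bias is 0 with no true effect. With a true effect of −2 points the estimate is about −1.87, a small error against the intervention.

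**Conclusion.** The point holds as an inconsistency in the stated primary analysis. Section 2.7 promises an analysis of all randomized patients and then fixes a complete-case comparison at week 10. In doing so it passes over week-5 PHQ-9 data that the trial collects and that section 2.11 says will be kept.

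The consequence is possible bias, in either direction, of a size that the documents do not determine. It is about 0.17 to 0.24 SD unadjusted, or 0.12 to 0.20 SD baseline-adjusted, if 20% of one arm and 5% of the other are lost from the worst scorers. It is about zero if rule and rate are the same in both arms. These figures rest on assumed loss rates, normal scores and assumed correlations of 0.5 and 0.7.

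It is worth correcting before follow-up is complete, because a week-10 questionnaire that was never requested cannot be recovered at analysis.

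**What to change.** 1. **Section 2.7.** Replace the exclusion sentence with, for example: *The primary analysis is a likelihood-based linear mixed model of PHQ-9 at baseline, week 5 and week 10. Baseline is treated as an outcome with a common mean across arms. Every randomized patient with at least one PHQ-9 score contributes, apart from data withdrawn at the patient's request. The between-arm contrast at week 10 is primary.* Treating baseline as an outcome matters: with baseline only as a covariate, a patient lost before week 5 would contribute nothing.
2. **Sensitivity analyses.** Report the complete-case analysis and a missing-not-at-random analysis, for example one that adds a range of penalties (delta) to unobserved week-10 scores, separately by arm.
3. **Sections 2.4, 2.7 and 2.11.** Reconcile them by stating that patients who stop sessions are still asked for the week-5 and week-10 questionnaires unless they withdraw consent. This concerns data collection only; the criteria for stopping are not at issue here.
4. **Abstract.** Align the model named there with section 2.7, saying which levels it refers to.

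The cost is slightly more analysis work and questionnaire follow-up of patients who stop attending. The model removes bias only when loss depends on scores that were observed, which is why the missing-not-at-random analysis is needed beside it.
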